## 13.3 Patient Accrual

This study will require a five-year accrual period with approximately 304 entries per year. The total duration of the study is expected to be thirteen years from the time the first patient is entered to the “final” overall survival analysis. If the average yearly accrual falls below 200 cases after 18 months, the feasibility of continuing the study will be discussed at the RTOG Data Monitoring Committee (DMC).

**13.3.1 Feasibility:** RTOG has an excellent history for successfully completing major Phase III prostate trials. One recently completed trial of significance is RTOG 94-13. It was a four-arm Phase III trial comparing definitive whole pelvic irradiation to irradiation to the prostate only and comparing neoadjuvant to adjuvant Total Androgen Suppression (TAS). Some of the eligibility requirements for participation in the study were: confirmed localized adenocarcinoma of prostate with an elevated PSA, estimated risk of lymph node involvement  $> 15\%$ , no involved common iliac or para-aortic nodes, pathological lymph-node-positive patients are ineligible, PSA  $\leq 100$  and no prior or concurrent hormonal therapy, radiation or chemotherapy. RTOG 94-13 opened for accrual on April 4, 1995 and closed to accrual on June 1, 1999. During that time period, 1323 men were entered with an accrual rate of 26.5 patients per month.

RTOG 94-08 is a two-arm study of endocrine therapy used as a cytoreductive and cytostatic agent prior to radiation therapy (RT) in locally confined adenocarcinoma of the prostate. Patients were randomized to receive either neoadjuvant TAS two months before or during RT, or to radiation therapy alone. Some of the eligibility requirements are: confirmed localized adenocarcinoma of prostate, clinical stage T1b-2b, no involved nodes, PSA  $\leq 20$  and no prior antiandrogen therapy, radiation, or chemotherapy, and no radical surgery or cryosurgery for the prostate. RTOG 94-08 was opened for accrual on October 31, 1994 and closed on April 30, 2001. As of April 30, 2001, there were 2028 patients entered with an accrual rate of 26 patients per month.

RTOG 94-06 was a dose escalation study of 3D conformal radiation therapy for prostate cancer from which the total dose for this proposed trial was to be chosen. Thirty-four institutions were credentialed by the Image-Guided Therapy (formerly 3DQA) Center (ITC) in St. Louis to participate in this trial and 28 of

these participated in the last two dose levels of RTOG 94-06. The average monthly accrual to RTOG 94-06, for patients whose eligibility is compatible with this proposed study, was 16.2 per month for dose level IV and 25.8 per month for dose level V. As 3D conformal radiation therapy becomes more widely used, more RTOG institutions will become credentialed by the ITC, and therefore, this proposed Phase III trial will have no problem reaching its targeted monthly accrual of 26 men.

#### **13.4 Analysis Plan (6/12/14)**

**13.4.1 *Statistical Methods:*** Gelman and Gaynor have shown that the Kaplan Meier method tends to overestimate cumulative failure probabilities for events with competing risks, such as time to PSA failure, disease-specific survival and time to distant metastases. Thus, the cumulative incidence approach will be used to estimate these endpoints as a function of time, since this approach specifically accounts for competing risks such as dying without a recurrence from prostate cancer. The distributions between the two arms will be compared by a method developed by Gray. Overall survival probabilities will be estimated by the usual Kaplan-Meier method. The survival distributions between the two arms will be compared using the log rank test. Factors associated with time to failure endpoints will be analyzed using the Cox regression model. Tumor control probability and normal tissue complication probability will be examined by categorical modeling techniques.

**13.4.2 *Interim Analysis to Monitor the Study Progress:*** Interim reports with statistical analyses will be prepared twice a year until the initial paper reporting the treatment results has been submitted.

In general, the interim reports will contain information about the patient accrual rate with a projected completion date for the accrual phase; data quality; compliance rate of treatment delivery with the distributions of important prognostic baseline variables; and the frequencies and severity of the toxicities by treatment arm. The interim reports will not contain the results from the treatment comparisons with respect to efficacy endpoints such as overall survival or PSA failure rate.

**13.4.3 *Significance Testing for Early Termination and Reporting:***

**13.4.3.1 *Primary Endpoint: Overall Survival***

Five interim significance tests of treatment difference are planned. The first interim analysis will be performed for the first RTOG semi-annual meeting after the 4th year of accrual. After the 5th year, it is projected that 100% of the target sample size has been achieved. The second interim analysis will be performed for the first RTOG semi-annual meeting one year after the last patient has been randomized. The third, fourth, and fifth interim analysis will be performed approximately eight, ten, and twelve years, respectively, from the start of the trial. The results will be reported to the NRG Oncology Data Monitoring Committee (DMC) with the treatment arms blinded.

The maximum number of deaths required for the study is 715. Under the alternative hypothesis given above, the projected numbers of deaths at the time of these five interim analyses are approximately 85, 186, 320, 478, and 640. The corresponding nominal significance level for each interim analysis will be 0.001. If the difference is significant at that level, the study statistician will recommend to the DMC that the randomization be discontinued (*if applicable*) and the study be considered for early publication.

At each planned interim analysis, the p-value from the log-rank test for assessing treatment efficacy, and the conditional power for the alternative hypothesis given the observed data will be reported to the NRG Oncology DMC. A low conditional power indicates a small probability of a significant treatment effect if future follow-up events are assumed to follow the same distribution under the alternative hypothesis. The responsible statistician may recommend early reporting of the results and/or stopping the trial if the treatment effect, with respect to overall survival, is highly significant, i.e. the p-value is less than the nominal value specified in a sequential design, or if the conditional power is less than 10%. Before making such a recommendation, the accrual rate, treatment compliance, safety of the treatments, and the importance of the study are also taken into consideration with the p-value and conditional power. The DMC will then make a recommendation about the trial to the group chair.

**13.4.3.2 *Secondary Endpoint: PSA Failure***

PSA failure will be a secondary endpoint of interest and will be reported early before the final overall survival result. The analysis of PSA failure will take place after the 7th year, approximately two years after accrual is completed. Pollack and his colleagues reported a five-year PSA-free failure rate of 69% for standard 70 Gy dose as compared to 79% for 78 Gy 3D-CRT. These results in the appropriate prognostic groups have been substantiated by Zelefsky and Hanks. The range of differences has varied from 10% to 25%. In light of Pollack's study, power was calculated for different hazard ratios for the analysis of PSA failure using the estimated sample size. The baseline PSA failure rate was

0.074 per year and was assumed to be constant over time. It was also assumed that the frequency of deaths without a PSA failure reported was 2% per year and was incorporated into Lakatos' method when calculating the number of PSA failures and statistical power. Table 3 below lists the number of PSA failures and power at the 7th year analysis time point for each hazard ratio ( $\Delta=1.3, 1.4, 1.45, 1.5$ , and  $1.57$ ). At the time of the PSA failure analysis, there will be at least 80% power to detect a hazard ratio greater than or equal to 1.4. The nominal significance level at this analysis is 0.025. The PSA results will be reported following this analysis. Treatment toxicity and quality of life (QOL) results will also be reported.

**Table 3. Power of significance testing for early reporting of PSA Failure**

| $\Delta$ | PSA Failures | Power |
|----------|--------------|-------|
| 1.30     | 338          | 67%   |
| 1.40     | 331          | 83%   |
| 1.45     | 326          | 90%   |
| 1.50     | 321          | 95%   |
| 1.57     | 316          | 98%   |

†Hazard ratio based on Pollack's results: 0.074 failure rate per year with standard dose compared to a 0.047 failure rate per year for 78.0 Gy 3D-CRT dose.

**13.4.4 *Analysis For Reporting the Initial Treatment Results: (9/18/03)*** This major analysis will occur after each patient has been potentially followed for a minimum of eight years for the primary endpoint, overall survival, and for a minimum of five years for the secondary endpoint, PSA failure, unless the early stopping rule is satisfied. It will include tabulation of all cases entered and those excluded from the analyses with the reasons for such given; the distribution of the important prognostic baseline variables; and observed results with respect to all the above mentioned endpoints. The primary hypothesis for the study is whether the higher total dose of 3D-CRT/IMRT will improve overall survival. All eligible patients randomized will be included in the comparison and will be grouped by assigned treatment in the analysis. The primary hypothesis of MTD 3D-CRT/IMRT treatment benefit will be tested using the Cox proportional hazard model with the major stratification factors included as fixed covariates. Additional analyses of treatment effect will include modifying factors such as age, race, and other patient characteristics. These analyses will also use the Cox proportional hazards model. The treatment comparison of time to PSA failure and disease-specific survival will be analyzed in a similar fashion. The treatment comparison of 2+ grade toxicity rates will use the z-statistic for testing binomial proportions. Also, where feasible, treatment comparisons with respect to time to PSA failure and overall survival will be compared within each ethnic category. Secondary analyses of the primary and secondary endpoints will be performed using the available Gleason scores from central review. Comparison of the proportion of patients with ED at one year by treatment arm will be performed using a chi-square test. Other comparisons will be made for subsets defined by the dose to the penis bulb and by age (<70 vs.  $\geq 70$  years old) respectively. Quality of life change scores from pretreatment to one year will be compared between treatment arms using a t-test. Quality of life will be correlated with responses on the IIEF. The z-test will be used to compare between treatment arms the average quality-adjusted survival within the first five years. An area under the curve analysis will be performed to compare the bowel and bladder symptoms assessed using FACE over the first five years.

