**The following questions will be asked at Study Registration:**

- \_\_\_\_\_ 1. Name of institutional person registering this case?
- \_\_\_\_\_ (Y) 2. Has the Eligibility Checklist (*above*) been completed?
- \_\_\_\_\_ (Y) 3. Is the patient eligible for this study?
- \_\_\_\_\_ 4. Date the study-specific Consent Form was signed? (*must be prior to study entry*)
- \_\_\_\_\_ 5. Patient's Initials (*Last, First*) [Initials only, effective 2/2002]
- \_\_\_\_\_ 6. Verifying Physician
- \_\_\_\_\_ 7. Patient's ID Number
- \_\_\_\_\_ 8. Date of Birth
- \_\_\_\_\_ 9. Ethnic Category (*Hispanic or Latino, Not Hispanic or Latino, Unknown*)
- \_\_\_\_\_ 10. Race
- \_\_\_\_\_ 11. Gender
- \_\_\_\_\_ 12. Patient's Country of Residence
- \_\_\_\_\_ 13. Zip Code (*U.S. Residents*)
- \_\_\_\_\_ 14. Patient's Insurance Status
- \_\_\_\_\_ 15. Will any component of the patient's care be given at a military or VA facility?
- \_\_\_\_\_ 16. Treatment Start Date
- \_\_\_\_\_ (N/Y) 17. Tissue/blood kept for cancer research?
- \_\_\_\_\_ (N/Y) 18. Tissue/blood kept for medical research?
- \_\_\_\_\_ (N/Y) 19. Allow contact for future research?
- \_\_\_\_\_ 20. Specify Gleason Score/PSA (*Gleason 2-6 and PSA  $\geq 10$  but  $< 20$  or Gleason 7 and PSA  $< 15$* )

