## 13.2 Sample Size

**13.2.1** *Stratification:* Patients will be stratified before randomization with respect to PSA and Gleason score: Gleason score 2-6 and PSA  $\geq 10$  but  $< 20$  vs. Gleason score 7 and PSA  $< 15$ , and Radiation Modality: 3D-CRT vs. IMRT. The treatment allocation scheme described by Zelen will be used because it balances patient factors other than institution. Patients will be randomized to MTD 3D-CRT or IMRT dose (79.2 Gy) vs. standard dose 3D-CRT or IMRT (70.2 Gy). (9/18/03)

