**13.2.2** *Sample Size Derivation:* The sample size calculations will address the specific primary hypothesis that the maximally tolerated dose of 3D-CRT/IMRT delivered to patients with localized adenocarcinoma of the prostate will result in a hazard reduction of 23% in the mortality rate. Roach et al. identified four prognostic risk groups using independent predictors of death: combined Gleason score (*centrally reviewed*), T stage, and pathologic lymph node status. These groups were defined by observing the correlation between these factors and disease-specific survival. The five, ten and fifteen-year overall survival rates by risk group are presented in Table 1 below. Based on these risk groups, the probability of surviving in a five-year interval (1-5, 6-10, 11-15) is shown in Table 2. A preliminary analysis of RTOG 94-08, which is a two-arm study of endocrine therapy used as a cytoreductive and cytostatic agent prior to radiation therapy (RT) in locally confined adenocarcinoma of the prostate, showed a five-year overall survival rate of 74% for patients with clinical stage T1b-T2b, combined Gleason scores 2-6 and PSA  $< 20$  treated with radiation therapy alone. Forty-four percent of the men entered on RTOG 94-08 had a combined Gleason score between 2-6 and a PSA value  $\geq 10$  but  $< 20$  while 56% had a Gleason of 7 and PSA  $< 15$ . In light of these data, the survival estimates based on Roach et al. risk group two were used for the sample size calculations. The five and ten-year overall survival rates used were 80% and 48%, respectively. The hazard rates of the control arm are assumed to be constant within each five-year interval (1-5, 6-10, and 11-15) and they are 0.0446, 0.1022, and 0.1386, respectively. Five interim significance tests and a final test are planned. Early testing will employ a nominal significance level of 0.001 while a level of 0.020 will be used at the final analysis to preserve a 0.025 level for the study. Using Lakatos' method for time-dependent mortality rates, 715 deaths are required to detect a survival benefit translating into a hazard ratio ( $\Delta$ ) of 1.3 with 90% statistical power using a one-sided test at a level of significance of 0.025. This level of 0.025 is the same as a level of significance that would be required for a two-sided test of significance at 0.05 to show the experimental arm is better than the control arm. Using the projected hazard rates for each five-year interval, we will require a total sample size of 1410 to be accrued uniformly over five years with an additional eight years of follow-up. Guarding against an ineligibility or lack-of-data rate up to 8%, **the final targeted accrual for this study will be 1520 cases.** Some of the secondary endpoints that will be evaluated are PSA failure, disease-specific survival, and quality-adjusted survival. The planned PSA failure analysis after the 7th year is discussed in more detail in section 13.4.3.2. (9/18/03)

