### 13.2.3 Erectile Function and Quality of Life

The International Index of Erectile Function Questionnaire (IIEF) is the primary measure for erectile function (ED). IIEF question number 1 (“How often were you able to get an erection during sexual activity?”) is scored from: none/almost never (*response 0-1*) or  $\leq$  half the time (*response 2-3*) to most times/almost always/always (*response 4-5*). A response of 0 to 3 on question number 1 of the IIEF will be considered erectile dysfunction. If the expected rate of ED at 12 months is 29%, then 688 patients per arm is sufficient for 90% statistical power and a two-sided significance level (0.05) to detect a reduction in ED to 19%. This assumes that 26% of the patients will have ED prior to the start of therapy and 80% compliance at 1 year. Only patients that respond 4-5 on question number 1 of the IIEF will be considered for this endpoint. The subset of patients age 70 and above will also be examined. Assuming 39% will have ED at 12 months, then this study will have the same statistical parameters to detect a reduction in ED to 25%, assuming that 50% of the sample is age 70 and above.

Quality of life will be measured using the Spitzer Quality of Life Index (SQLI). A 0.5 point difference in SQLI scores has been shown to be clinically meaningful, assuming a standard deviation of 0.54 for SQLI. If ED reduces quality of life, then the difference in quality of life between the arms only may occur in this subgroup. In addition, ED may cause a reduction in quality of life greater than the minimally important difference; assuming the effect is 50% greater, then a 0.75 difference is expected. However, only those patients with ED may substantially impair quality of life. Therefore, the proportion of patients with ED may reduce the observable difference in quality of life. Using the above estimates of ED and sample size, this study will have 90% statistical power to find an observable difference of 0.12 in SQLI between the two arms with a significance level of 0.05 (*two-sided*).

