### 13.5 Inclusion of Minorities

In conformance with the national Institutes of Health (NIH) Revitalization Act of 1993 with regard to inclusion of women and minorities in clinical research, we address this issue here, as we will also analyze treatment differences in this male cohort by ethnicity. Based on previous RTOG prostate protocol data the minority enrollment for this study is expected as follows:

| Ethnic Group                              | Number      | Percent (%) |
|-------------------------------------------|-------------|-------------|
| American Indian or Alaskan Native         | 3           | 0.2         |
| Asian                                     | 8           | 0.5         |
| Black or African American                 | 228         | 15.0        |
| Hispanic or Latino                        | 46          | 3.0         |
| Native Hawaiian or other Pacific Islander | 4           | 0.3         |
| White                                     | 1216        | 80.0        |
| Other/Unknown                             | 15          | 1.0         |
| Total                              | 1520 | 100  |

Obviously with 80% of the available sample being white, univariate comparisons by treatment will not yield sufficient power in most cases. We will, however, also include the ethnicity variable in all regressions including the Cox model.

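### The primary survival model in 13.4.4 leaves age to additional analyses; adding it would gain about 1 to 9 points of power, depending on an age effect the protocol does not give

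*Protocol*

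**What the plan says.** - **Primary test (13.4.4).** The hypothesis of a survival benefit "will be tested using the Cox proportional hazard model with the major stratification factors included as fixed covariates".
- **Stratification factors (13.2.1).** "Patients will be stratified before randomization with respect to PSA and Gleason score" in two groups, and by 3D-CRT versus IMRT. Age is not among them.
- **Place of age (13.4.4).** "Additional analyses of treatment effect will include modifying factors such as age, race, and other patient characteristics". Race is listed beside age here.
- **Ethnicity (13.5).** The protocol will "also include the ethnicity variable in all regressions including the Cox model". Taken literally, this puts ethnicity in the primary model, which 13.4.4 does not list.
- **A second survival comparison (13.4.1).** "The survival distributions between the two arms will be compared using the log rank test". Section 13.4.3.1 uses the log-rank test at the interim analyses.
- **Availability of age (Eligibility Checklist).** The registration questions include "8. Date of Birth".
- **Age mix (13.2.3).** The erectile function calculation is made "assuming that 50% of the sample is age 70 and above". No age SD and no relation between age and mortality are given.
- **Levels (13.2.2).** "Early testing will employ a nominal significance level of 0.001 while a level of 0.020 will be used at the final analysis".

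**The concern.** The endpoint counts every death, and half the men are assumed to be 70 or older. The control arm is planned to have 48% survival at ten years, with a hazard rising from 0.0446 to 0.1386 per year across the three five-year intervals. Section 13.4.3.2 assumes 2% per year die without a reported PSA failure, which is 0.02/0.0446 = 45% of the control hazard in years 1-5. So a good part of early mortality is planned to occur without PSA failure, and age is a natural predictor of it.

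In a Cox model, leaving out a strong predictor of the outcome pulls the treatment hazard ratio towards 1 even when the arms are balanced, and the test loses some power compared with a model that includes it. Age is already collected, so the protocol forgoes precision that needs no new data. The covariate list is also not settled across 13.4.1, 13.4.4 and 13.5, so the wording needs attention anyway.

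**Working it through.** **Step 1. Reproduce the design.** Inputs from 13.2.2: 1410 men, uniform accrual over 5 years plus 8 years of follow-up, control hazards 0.0446, 0.1022 and 0.1386 per year, hazard ratio 1/1.3 = 0.77. Allocation of 1:1 is assumed.

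Control survival: exp(-5 × 0.0446) = 0.80 at five years; 0.80 × exp(-5 × 0.1022) = 0.48 at ten. Both match.

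Expected deaths at time t are the sum over arms of 705 × the average of [1 - S(t - u)] over entry times u. At 13 years this gives 714, against the stated 715. At 4, 6, 8, 10 and 12 years it gives 84, 185, 319, 477 and 639, against 85, 186, 320, 478 and 640. The design is reproduced.

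**Step 2. Power of 715 deaths with no age term.** By Schoenfeld's formula the expected Z is √715/2 × ln 1.3 = 13.37 × 0.2624 = 3.51. At one-sided 0.020 (critical value 2.054), power is Φ(3.51 - 2.054) = 92.7%. Deaths needed for 90% at that level are 4 × (2.054 + 1.282)²/(ln 1.3)² = 647. So 715 deaths are not too few for the planned 90% under a population hazard ratio of 1.3.

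**Step 3. Effect of an age term.** Age was simulated as a normal covariate under the stated hazards, with 1500 trials per setting, a cut at 715 deaths and one-sided 0.020. The Cox model was fitted with arm alone and with arm plus age; Gleason/PSA group, modality and ethnicity were not simulated. The ratio of 1.3 was applied at fixed age. Power is taken from the mean Z; the gain in observed rejection rates agreed within about 0.7 points. All age effects and SDs are assumptions.

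| HR per year of age | Age SD (years) | Without age | With age | Gain (points) |
|---|---|---|---|---|
| 1.04 | 6 | 91.2% | 92.3% | 1.1 |
| 1.05 | 6 | 91.6% | 93.1% | 1.5 |
| 1.05 | 7 | 90.9% | 92.9% | 2.0 |
| 1.06 | 7 | 88.9% | 92.1% | 3.3 |
| 1.07 | 7 | 88.4% | 92.8% | 4.3 |
| 1.08 | 7 | 86.7% | 92.3% | 5.5 |
| 1.09 | 7 | 85.6% | 92.7% | 7.1 |
| 1.105 | 7 | 82.9% | 92.1% | 9.2 |

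Gains are differences of unrounded powers. The spread in the adjusted column is simulation error around the 92.7% of step 2. A separate set of simulations gave about 1, 2, 3, 5-6 and 8 points at log-hazard SDs of 0.24, 0.34, 0.41, 0.54 and 0.65, which agrees.

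**Step 4. The other reading of 90%.** Suppose the planned 90% is the power without age. Let k be the ratio of mean Z with age to mean Z without. Adjusted power is then Φ(k × (2.054 + 1.282) - 2.054). In the weakest setting k = 1.021 and power is 91.2%; in the strongest k = 1.154 and power is 96.4%. The gain is 1.2 to 6.4 points.

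**Step 5. Chance imbalance in age.** With 705 men per arm and SD 7, the standard error of the difference in mean age is 7 × √(2/705) = 0.37 years. At 8% per year this moves the log hazard ratio by 0.37 × ln 1.08 = 0.03, against a target of ln 1.3 = 0.26.

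**The case against.** The strongest reply is that nothing here is in error. A Cox model adjusted for the stratification factors is conventional, prespecified and valid, and the same section already promises analyses that include age. All of that stands. What it leaves is that an additional analysis does not carry the primary conclusion, so the precision from age is not used where the decision is made.

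Four stronger readings are tempting, and the documents do not support them.

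- **That the primary model adjusts for two factors alone.** Section 13.5 puts ethnicity in all regressions. Nor are the listed factors unrelated to death: 13.2.2 names Gleason score among the predictors of it.
- **That the trial falls short of its planned power.** The 1.3 in 13.2.2 is set on population survival rates with no age term. The lower unadjusted figures in step 3 arise because 1.3 was taken there as the ratio at fixed age, and a Cox hazard ratio changes when a covariate is averaged over. Against the planned population effect, 715 deaths give 92.7%.
- **That a definite loss can be stated.** The protocol gives no age effect, so any narrow figure comes from the analyst's assumption.
- **That imbalance threatens the result.** Step 5 shows a typical imbalance is small, and the type I error rate already allows for it.

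A last objection concerns timing. Section 13.4.5 says the early interim analyses are done, and their comparisons went to the data monitoring committee. Changing the monitoring statistic now would be neither simple nor clean. This is right, and it limits the change to the final analysis.

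**Conclusion.** The point holds as one of efficiency. The primary Cox model omits a baseline variable that is recorded for every man and plausibly predicts the endpoint. Including it would add about 1-2 points of power if the age effect is weak (hazard ratio 1.04-1.05 per year), 3-7 points if moderate (1.06-1.09, SD 7), and about 9 if strong (1.105). If 90% is read as the power without age, the same range gives 1.2 to 6.4 points.

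For scale, matching the adjusted test without age would take 715 × (k² - 1) extra deaths: about 30 in the weakest setting and about 120 at 1.07 per year (k = 1.081). The step from the fifth interim to the final analysis is 715 - 640 = 75 deaths.

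The direction is secure provided age predicts death. The size rests wholly on the assumed age effect and SD. Type I error and the planned 90% are not in question. Separately, 13.4.1, 13.4.4 and 13.5 do not agree on a single model for the survival comparison and should be made to.

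**What to change.** Before the final analysis, and decided by people blinded to results by arm:

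1. State in 13.4.4 one primary Cox model: arm + Gleason/PSA group + radiation modality + age as a continuous covariate. Zubrod 0/1 is optional; no gain from it was calculated.
2. Keep the model without age as a named sensitivity analysis.
3. Say in 13.4.4 and 13.5 whether ethnicity is in the primary model, and in 13.4.1 what role the log-rank test has at the final analysis.
4. Leave the interim log-rank tests and the futility boundaries in 13.4.5 unchanged. Read as one-sided levels, the interim and final levels sum to 5 × 0.001 + 0.020 = 0.025, so the overall level is held whatever the correlation between the interim log-rank and final Cox statistics.

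The cost is an amendment of wording and documentation of who decided and what they had seen. No new data are needed. The reported hazard ratio becomes conditional on age, so it is not directly comparable with the population ratio of 1.3 used in planning; the sensitivity analysis covers that.
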